### Outcome measures

An overview of all measures in given in Fig. 3.

**Fig. 3 Fig3:**
[figure not shown]
Schedule of enrolment, interventions, and assessment. Adapted from SPIRIT figure 2013

#### Cognitive functioning

The Dementia Ratings Scale-2 (DRS-2) [22] will be used at baseline to asses overall level of cognitive functioning and after the six-month intervention period to monitor cognition during the six-month intervention period in the persons with aMCI. The DRS-2 assesses multiple cognitive domains and helps to distinguish individuals with aMCI from patients with Alzheimer’s dementia and healthy controls [23].The CogState, a computerized cognitive assessment, will be used to monitor more specific cognitive domains at baseline and after the six-month intervention period in the person with aMCI. CogState is sensitive to cognitive aging effects in MCI and dementia and therefore to interventions that remediate these effects [24]. The following subtasks of the CogState will be used: Detection task – a simple reaction time paradigm that measures psychomotor function; Identification task – a choice reaction time paradigm that measures visual attention; One Card Learning task – a continuous visual recognition learning task that assesses visual recognition memory and attention; One Back task – a task that assesses working memory and attention.The Rey Auditory Verbal Learning Test (RAVLT) [25, 26] will be administered to assess declarative memory. A 15-word list will be read to the participants, after which they will be asked to repeat all words they remember. This will be done five times. After 30 min, a delayed recall and recognition trial will be conducted.The Word Stem Completion Test (WSCT) [27] will be administered to assess priming memory. A word completion method similar to the method used in previous studies [28, 29] will be used.The Mirror-Tracing Task (MTT) [30] will be used to asses procedural memory. Participants are asked to trace the cutout outline of a five-point star without touching the edges of the star while looking in a mirror. Their direct view of their own hand and the figure to be traced will be blocked. Testing consists of two blocks of five trials, separated by an interval of 15 min.The Serial Reaction Time Task (SRTT) will be administered as a procedural memory task that involves only a limited motor component. The SRTT was developed largely based on the SRTT used in previous research [31] and will be administered on an Android-run tablet (Samsung SM-T580NZWAXAR 10.1 Galaxy Tab A T580) using OpenSesame Software [32].At baseline, the Wide Range Achievement Test 4 (WRAT4) [33] reading subtest will be administered to assess the patients’ reading achievement and cognitive reserve. Participants read aloud a list of 55 words that increase in complexity throughout the task and 1 point is awarded for each correctly pronounced word. Previous studies have successfully utilized reading ability as a measure of cognitive reserve [34].

#### Functional status

All measures of functional status will be conducted at baseline and after the six-month intervention period.The study partners will be asked to fill out the Everyday Cognition (E-Cog) [35] about the individuals with aMCI’s functioning in instrumental activities of daily living (IADLs). The E-Cog is an informant-based measure that assesses the participant’s ability to perform everyday tasks in the following areas: memory; language; visuospatial abilities; planning; organization; and divided attention.The study partners will be asked to fill out the Functional Assessment Questionnaire (FAQ) [36] about the person with aMCI’s functional status. The FAQ is the standard functional measure required for use throughout the Alzheimer’s Disease Research Center network.The study partners will be asked to fill out the Treatment Diffusion Log about the person with aMCI’s and their own time spent on any type of physical exercise, computerized cognitive training, wellness behaviors, use of a calendar, and supportive therapy. This will be done to assess specific skills targeted by the interventions.The Memory Compensation Training Therapists will fill out the MCT Adherence Questionnaire about the person with MCI’s use of the calendar. This questionnaire assesses how well an individual utilizes the sections of the MCT calendar system. The evaluator will examine MCT compliance for two randomly selected days from the prior week. This will be done on the first day of treatment, as well as during the booster session.The Memory Compensation Training Therapists will also be asked to determine the MCT Training Score on the final day of the program This 0–6 score reflects the individual with MCI’s progress in the three phases of calendar training. A score of 0 reflects no progress while a score of 6 reflects mastery of all three training phases. Intermediate scores (1–5) reflect intermediate levels of training progress.The Short Physical Performance Battery (SPPB) [37] will be administered to the individuals with aMCI to monitor their physical performance. This includes a timed 8-ft walk, standing side by side, semi-tandem and full-tandem stance, and a timed arms-folded rise from seated to standing.

#### Quality of life, mood, and anxiety

The quality of life, mood, and anxiety measures will be conducted at baseline and after the six-month intervention period.Both the persons with aMCI and the study partners will be asked to complete the Quality of Life-AD (AD-QOL) [38] at baseline and after six months. The AD-QOL is a 13-item measure developed for individuals with dementia that has been utilized in aMCI and with study partners. Individuals with aMCI and study partners rate their relationships, concerns about finances, physical condition, mood, energy level, memory, aspects of daily functioning, and overall life quality on a four-point scale.Both individuals with aMCI and study partners will be asked to complete the Center for Epidemiologic Studies Depression Scale (CES-D), a well validated 20-item self-report measure of depressive symptoms with a four-factor structure consisting of negative affect, lack of positive affect, somatic symptoms, and interpersonal difficulties subscales [39].Both the persons with aMCI and the study partners will complete the REACH Anxiety Inventory Form (REACH-AIF) [40], a 10-item rating scale modified from the State-Trait Anxiety Inventory, by the Resources for Enhancing Alzheimer’s Caregiver Health (REACH) project [41].

#### Self-efficacy

The persons with aMCI will be asked to complete selected (based on their relevance to memory-based daily activities) items from the Chronic Disease Self-Efficacy Scales [42]. The language from the original scales was modified to be specific to memory (i.e. “your memory/cognition” rather than more general references to “your health condition”). The result is the nine-item Self-Efficacy in Memory in MCI scale (memSE).Study partners will be asked to complete the Caregiving Competence and Mastery Components (CCMC) of the Pearlin [43]. These measures reflect their titles and are in the range of 4–6 items.

#### Attitudes towards research

Barriers to Research Participation Questionnaire (BRPQ) [44]: Both the persons with aMCI and the study partners will be asked to complete the BRPQ at baseline. BRPQ is a 17-item screener that assesses attitudes towards research participation. This scale assesses five predictors of study participation (i.e. mistrust, religious beliefs, health beliefs/fears, role overload/time demands, and perceived personal and community benefits).

#### MRI acquisitions

All images will be acquired using a 3-T MRI scanner (Siemens Prisma) that is controlled for quality and are monitored weekly. We will use imaging to assess the efficacy and to elucidate the mechanisms of intervention impact by measuring brain changes over the intervention period. The primary imaging outcomes will be structural MRI (sMRI), arterial spin labeling (ASL), and resting state fMRI. Diffusion tensor imaging (DTI) will also be acquired. In addition, we will also ascertain the degree of vascular pathology using fluid-attenuated inversion recovery (FLAIR) and susceptibility-weighted MRI. The detailed imaging protocol and imaging measures are described in the supplementary neuroimaging protocol, which can be found in Additional file 1.

### Data management

An online REDCap database will be used, supported by Mayo Clinic Jacksonville. To ensure high-quality data, we will use double-data entry for 20% of the participant couples, randomly selected at each site. If data entry consistency is < 95%, all data will be entered using double-data entry. There will also be a range check in place for each measure.

### Statistical methods

The primary analyses will use linear mixed effects models to examine change from baseline to post intervention (~ 6 months) in each of the outcomes. These models control for within-subject effects through the use of per-subject random effects for slopes and intercepts over the six-month follow-up period. We will estimate the degree of change over time in each of the specific measurement intervals within randomized groups and test for differences in these changes between groups while conforming to linear model assumptions. We will evaluate the assumptions required for the appropriate use of linear models and will apply any needed transformations in the data to conform to the model assumptions. Analyses will be conducted to assess the aims listed above. In addition, to make it possible to identify which individuals are most likely to benefit from the interventions, we will incorporate variables to evaluate whether variables either attenuate or modify cognitive or imaging changes. Additional analyses are currently unknown. Missing data will be handled based on what appears to be most appropriate for the analysis being conducted. No interim analyses will be conducted.

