##### Power and sample size

In our analyses of the imaging measures over the six-month intervention period, we expect that treatments will reduce age-dependent changes, measured as percent reduction in change from baseline, i.e., effect size (Cohen’s d). Using pilot data, we calculated means and standard deviations (SD) of changes in imaging variables as estimates for the non-treatment group. As in Aim 1, roughly 120 participants per group would be needed to detect an effect size of 0.325 with 80% power and α = 0.05. These effect sizes correspond to reductions in age-related imaging changes of roughly 30% or 50%. The present trial will also allow us to begin building towards those trial sizes.

#### Aim 2

To estimate effect sizes regarding the impact of computerized cognitive training, yoga, or an active control (wellness education) delivered in a multicomponent program that provides memory compensation and support groups to all subjects on cognitive function, daily function, mood, anxiety, and quality of life in persons with aMCI. We hypothesize that cognitive function, daily function, mood, anxiety, and quality of life will be higher in the computerized cognitive training and the yoga groups than in the active control group.

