##### Power and sample size

Meta-analysis of studies of cognitive impact in healthy older adults suggest Cohen’s d within groups was 0.325 for aerobic exercise and 0.327 for cognitive training [18]. A power analysis in Gpower assuming two independent means indicated 118 people per arm are necessary to have 80% power to detect this magnitude of a difference between samples. Due to the group-randomized nature of the current trial, it is possible that a higher n is required. The scope of this pilot funding opportunity limits us to just 25 aMCI patients and their 25 partners per arm, leading to a total of 75 aMCI patients and their 75 partners. The results of the current trial may serve as pilot data for future studies.

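### The between-arm comparison of change from baseline should be adjusted for the baseline value, which is already collected; this costs nothing and makes the pilot's effect sizes more precise

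*Protocol article*

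**What the plan says.** The Statistical methods section of the protocol article describes linear mixed models that "examine change from baseline to post intervention (~ 6 months) in each of the outcomes", with per-subject random intercepts and slopes. Differences in these changes are tested between the randomised groups, and the same section says the analyses serve the listed aims. It mentions other variables that may modify cognitive or imaging changes. It does not say that the baseline value of the outcome is a covariate, or that baseline means are held equal across arms.

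The effect is described in three other places:
- **Aim 2** expects that outcomes "will be higher in the computerized cognitive training and the yoga groups than in the active control group".
- **Power and sample size under Aim 1** describes the imaging effect as "measured as percent reduction in change from baseline, i.e., effect size (Cohen’s d".
- **Power and sample size under Aim 2** starts from a meta-analysis in which "Cohen’s d within groups was 0.325 for aerobic exercise and 0.327 for cognitive training". It then gives a between-sample calculation with power set at 80%: "A power analysis in Gpower assuming two independent means indicated 118 people per arm are necessary".

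None of these places names the SD that standardises Cohen's d. Under Outcome measures, the DRS-2, CogState, quality of life, mood and anxiety are measured at baseline and again after the six-month intervention period.

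**The concern.** Effect sizes for a larger trial are a declared product of this pilot, so their precision matters. A between-arm comparison of change subtracts the whole baseline value from the six-month value. If r is below 1 and the SD is the same at both visits, that over-corrects: an arm that starts low by chance tends to gain more, whatever its treatment. Baseline adjustment subtracts only the part of the baseline value that predicts the outcome.

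The Randomization and blinding section allocates nine sessions, three per arm, with about 25 couples per arm. With so few units, chance differences at baseline are plausible. The unadjusted change analysis would carry part of them into the estimated effect and widen its interval.

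There is a lesser, related point. A Cohen's d can be used to size the next trial only if its SD is known, and the word *higher* in the Aim 2 hypothesis sits loosely beside an analysis of change.

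**Working it through.** **The plan's own figure.** With d = 0.325 and 80% power, a one-sided 5% test of two independent means needs 2 × (1.645 + 0.842)² / 0.325² = 117.1, so 118 per arm. The t-test calculation gives 117.7, also 118. The stated 118 is therefore reproduced, on a one-sided basis that the protocol does not state; two-sided, the t-test calculation gives 150. The calculation is the same whether the two means are six-month scores or change scores, so it does not settle which is meant.

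**Inputs for the comparison.** Two visits, about 25 people per arm and three sessions per arm come from the protocol. The correlation r is not given, so a range is assumed. The SD is taken as equal at both visits (σ = 1). Sessions are ignored at first.

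**Variance per person**
- Change: 2(1 − r)
- Baseline-adjusted: 1 − r²
- Ratio, adjusted to change: (1 + r)/2, so the reduction is (1 − r)/2

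| r | change | adjusted | reduction |
|---|---|---|---|
| 0.5 | 1.00 | 0.75 | 25% |
| 0.7 | 0.60 | 0.51 | 15% |
| 0.8 | 0.40 | 0.36 | 10% |

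The direction does not depend on equal SDs. With SDs σ₀ at baseline and σ₁ at six months, the change variance exceeds the adjusted variance by (σ₀ − rσ₁)², which is never negative. Estimating the slope costs a little in a small sample.

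**Interval width at 25 per arm.** The half-width is 1.96 × √(2 × variance / 25). At r = 0.7 it is 1.96 × √0.048 = 0.43 SD for change and 1.96 × √0.0408 = 0.40 SD adjusted. At r = 0.5 the figures are 0.55 and 0.48.

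**Chance imbalance.** Ignoring sessions, the standard error of the baseline difference between two arms is √(2/25) = 0.28 SD. Given a baseline difference D, the change contrast is shifted by −(1 − r)D. With D = 0.28 and r = 0.7 the shift is 0.3 × 0.28 = 0.08 SD, about a quarter of 0.325. The adjusted contrast has no such shift in expectation.

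**Sessions.** Let τ² be session variance that baseline does not explain. The variance of an arm mean is then τ²/3 + (person variance)/25. For illustration at r = 0.7:
- τ² = 0.02: 0.0067 + 0.0240 = 0.0307 for change, against 0.0067 + 0.0204 = 0.0271 adjusted, a reduction of about 12%.
- τ² = 0.05: 0.0407 against 0.0371, a reduction of about 9%.

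Both are below the 15% without session variance.

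**Why the SD must be named.** The conversion is d on the change scale = d on the score scale / √(2(1 − r)). A raw difference of 0.325 score SDs is 0.275 change SDs at r = 0.3, 0.325 at r = 0.5, 0.420 at r = 0.7 and 0.514 at r = 0.8.

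**The case against.** The strongest reply is that a difference in change from a mixed model is a standard, valid analysis under randomisation, and that baseline covariates or constrained baseline means are often left to an analysis plan that is not shown here. Both statements are fair. The analysis is not wrong, and the analysis plan may already contain the adjustment. But the article does state its contrast, and a better one is available from the same data. With complete data, two visits and free baseline means, the stated model reduces to a change-score comparison.

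It can also be said that the percentages ignore clustering and rest on an assumed r. That stands: 10% to 25% is a person-level figure, not this trial's gain.

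A reader might go further and infer three things that the documents do not support:
- **That the power calculation defines a difference in score level.** Two independent means fit change scores equally well, the input is a within-group d, and the Aim 1 text uses the same 0.325 for change from baseline. Only the word *higher* in the Aim 2 hypothesis points to a level, and that sentence states an expected direction.
- **That the effect size has two different values.** No section reports two values. Under randomisation the raw contrasts in level and in change have the same expectation.
- **That the next trial would be mis-sized by a large factor.** The gap between the two scales depends on r, is zero at r = 0.5 and reverses below it.

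**Conclusion.** The point holds as a free improvement, not as an error. The stated comparison of change is valid but gives up precision that the baseline data would supply: about 25%, 15% or 10% of the person-level variance at r = 0.5, 0.7 or 0.8. This assumes equal SDs at both visits and complete data, and it ignores sessions. With session variance that baseline does not explain, the gain is smaller. Three sessions per arm also make chance baseline imbalance plausible, which is a further reason to adjust. The unnamed SD and the word *higher* would be minor matters of detail alone; they belong here because the same edit settles them and makes the pilot's effect sizes usable for planning.

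**What to change.** In Statistical methods, for Aims 1A and 2, define the estimate as the between-arm difference in the six-month value adjusted for the baseline value of the same measure, with a 95% CI. Either baseline as a covariate or a mixed model with baseline means constrained equal across arms will do. State the SD used for Cohen's d, for example the pooled baseline SD. Report r and the SD of change for each outcome, so that a later trial can convert between scales. Reword the Aim 2 hypothesis to refer to the same contrast. If the analysis plan already adjusts for baseline, a sentence saying so in Statistical methods is enough for that part.

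The cost is a few sentences. No new data or visits are needed, and the only statistical price is one estimated slope per outcome.

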### Participants

Our target is to have a total of 75 couples, recruited approximately evenly across the three sites. Enrollment will happen in dyads (i.e., a person with aMCI and a healthy study partner). Twenty-five dyads will be assigned to each treatment arm. Once written informed consent is obtained, participants will be screened for their eligibility over the phone. The Clinical Dementia Rating scale (CDR) [19] will be used to confirm the aMCI status of the patient and the Telephone Interview for Cognitive Status for Memory (TICS-M) will be used to confirm study partners are cognitively healthy. Specific inclusion and exclusion criteria are outlined in Table 1.

**Table 1 Tab1:** Inclusion and exclusion criteria

Inclusion criteria	Exclusion criteria
For the person with aMCI: 1. Written informed consent for participation. 2. A formal diagnosis of amnestic mild cognitive impairment [1] (single domain or multidomain) in the last 6 months (by neuropsychological evaluation) OR A CDR score of 0 or 0.5 and a TICS-M score of at least 25 on the TICS-M. 3. Aged at least 50 years. 4. Either not taking or stable on nootropic(s) and/or pain medication on a dose and frequency that affects cognitive abilities for at least 3 months. 5. Fluent in English. For the study partner: 6. Written informed consent for participation. 7. Aged at least 21 years. 8. A score of at least 32 on the TICS-M 9. Study partner has at least twice-weekly contact with the participant.	For the person with aMCI: 1. MRI contraindications (e.g. ferrous metal in the body, claustrophobia, pregnancy) For both the person with aMCI patient and study partner: 2. Physical impairments, language comprehension deficits, or significant hearing disturbances that would limit ability to perform tasks or participate in the intervention

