### Randomization and blinding

The group nature of intervention allows participants to compare their experiences, so individualized randomization poses a risk for diffusion of treatment effects. However, the group format limits in the ability to randomize per couple. Thus, we will block randomize by group instead of by participant assuring equal randomization of sessions to each of the three arms of the trial at each site. In other words, everyone in the first intervention period will receive the same treatment determined at random. The next intervention group will receive one of the two remaining arms also determined at random. The study biostatistician will randomize using a computerized random number generator to determine initial and second sessions at each site. The biostatistician is not involved in recruitment, assessment, or intervention delivery in any way. Due to the nature of the intervention, participants cannot be blinded. However, to mitigate selection bias, patients as well as study staff will be kept blind until recruitment for each session has been completed. Sessions will be offered sequentially three times in year 1 and include 6–12 individuals with aMCI and study partner couples per session. Hence, there will be the opportunity to block randomize nine (three sites × 3) sessions involving approximately 25 couples per arm for a total of 75 participants. A flow chart diagram showing summary of the pilot trial design can be found in Fig. 1.

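### Sessions are randomised in blocks by site, but the primary model as described controls only for subject effects, so arms are not compared within the site blocks

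*Protocol article*

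**What the plan says.** The Randomization and blinding section of the protocol article makes the session the unit of allocation and the site the block. The stated intention is to "block randomize by group instead of by participant assuring equal randomization of sessions to each of the three arms of the trial at each site". Each arm is therefore given once at each of three sites. The same section plans to "block randomize nine (three sites × 3) sessions involving approximately 25 couples per arm", and sessions "include 6–12 individuals with aMCI and study partner couples per session". The Participants section adds that couples are "recruited approximately evenly across the three sites".

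The Statistical methods section then states what the primary linear mixed models control for: "These models control for within-subject effects through the use of per-subject random effects for slopes and intercepts over the six-month follow-up period". Change is estimated within randomised groups and compared between them. The section also mentions further variables that may attenuate or modify change, but only to identify who benefits, and it names none of them. Site and session do not appear. The Aim 2 power paragraph concedes that group randomisation may call for more participants, but this is not carried into the description of the model.

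**The concern.** Blocking by site fixes the number of sessions per arm at a site, not the number of people. With sessions of 6 to 12 couples, one arm can draw up to twice as many participants from a given site as another arm does. A subject-level intercept removes differences in level between sites. It does not remove differences between sites in six-month change, and change is what is analysed.

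Two things follow if the model is run as described. With balanced sessions, site cancels from the contrast but stays in the residual, so the standard error is too large. With unbalanced sessions, part of any site difference enters the realised contrast, and the standard error does not allow for it. The main product of this pilot is a set of effect sizes for planning a larger trial, so both the estimate and its interval should reflect how allocation was done.

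**Working it through.** **Inputs from the article.** Three sites, nine sessions, each arm once per site, 6 to 12 couples per session, about 25 couples per arm and per site (mean 25/3 = 8.3 per session), and a reference effect of d = 0.325.

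**Assumptions, because the article gives no variance for site or session.** Units are the within-session SD of change. The between-site SD is 0.5, so site is 0.25/1.25 = 20% of the variance when there is no session effect. The between-session SD is 0, 0.23 or 0.33, so session ICC = 0.23²/(1 + 0.23²) = 0.05 or 0.33²/(1 + 0.33²) = 0.10.

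**Step 1. The plan's own figure.** The 118 per arm reproduces as 2(1.645 + 0.842)²/0.325² = 117.1, rounded up, which is a one-sided 5% test (two-sided: 149). It treats participants as independent, so it carries no allowance for site or session. The 0.325 serves below only as a yardstick.

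**Step 2. How much of a site difference can enter the contrast.** The shift is the difference between two arms in the share of couples from a site, times the site difference in change.
- Equal sessions: share difference 0, shift 0.
- Extreme layout, arms 12/6/7, 6/12/7 and 7/7/11 over the three sites. Every arm and site totals 25 and every session lies within 6 to 12. The share difference is (12 − 6)/25 = 0.24 at site 1 and −0.24 at site 2. If those two sites differ by 0.5 SD, the shift is 0.24 × 0.5 = 0.12 SD.
- Session sizes drawn uniformly from 6 to 12, one site differing by 0.5 SD (200,000 draws): mean shift 0.00, SD 0.043, 95th percentile of the absolute shift 0.084. A shift of 0.12 or more occurs in about 0.3% of draws.

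The sampling SE of an arm difference at 25 per arm is √(2/25) = 0.283. The typical shift is therefore 0.043/0.283 = 0.15 SE, and the extreme one 0.12/0.283 = 0.42 SE.

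**Step 3. Standard error without site, no session effect.**
- Near-equal sessions: the expected residual variance is 1 + (75 × 2/3 × 0.25)/72 = 1.174, so the model SE is √(0.08 × 1.174) = 0.306 against a true SD of 0.283. The SE is too large.
- Extreme layout: the true SD is √(0.08 + 2 × 0.24² × 0.25) = 0.330, against a model SE of about 0.306. The SE is too small.

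**Step 4. Type I error of a nominal two-sided 5% test.** Simulation of change scores, 75 couples, 40,000 trials per row, site SD 0.5:

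| Layout | Session SD | No site | Site only | Session means, arm + site (4 df) |
|---|---|---|---|---|
| Near-equal (8 or 9) | 0 | 3.5% | 4.8% | 5.0% |
| Near-equal | 0.23 | 7.5% | 9.6% | 4.8% |
| Near-equal | 0.33 | 11.7% | 14.5% | 4.9% |
| 12/6/7, 6/12/7, 7/7/11 | 0 | 6.4% | 5.0% | 5.1% |
| same | 0.23 | 11.1% | 9.6% | 4.9% |
| same | 0.33 | 14.9% | 13.9% | 4.8% |

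Repeat runs gave up to 3.9% and 7.0% for the two no-site entries with session SD 0.

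**Step 5. Why site alone fails.** With session SD 0.23 and near-equal sessions, the true SD of the contrast is √(0.08 + 2 × 0.23²/3) = 0.340, but the site-only model reports about 0.286. Each site-by-arm cell holds one session, so session variation is the site-by-arm residual, with 9 − 1 − 2 − 2 = 4 df.

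**The case against.** The strongest reply is that the article lists no fixed effects at all. It is a condensed account, and a covariate list that includes the blocking factor is commonly left to the full protocol or the analysis plan, neither of which is shown. That stands to this extent: nobody can say from the article that the full plan omits site. But the text is not silent on structure. It says what the models control for, and everything it names is at subject level, while the allocation it describes is by session within site.

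A reader might infer that site systematically biases the arm comparison. The documents do not support this. Arms are assigned at random within site, and "patients as well as study staff will be kept blind until recruitment for each session has been completed". Session size should therefore be largely unrelated to arm, and the shift averages zero. The arm of a site's third session can be worked out by elimination, but nothing in the article shows that this affects session size.

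A reader might also set the 0.12 SD shift against the 0.325 reference effect (37%) and treat that as the expected damage. It needs opposite 12/6 splits at two sites and an assumed 0.5 SD site difference in change. It is also well inside the sampling error of a pilot that the article says is too small to detect 0.325.

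Finally, the precision loss with balanced sessions is conservative and creates no false positives. That is true only if sessions do not vary. With session ICC of 0.05 to 0.10 the model without site runs above its nominal level (7.5% to 11.7% with near-equal sessions).

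**Conclusion.** The point holds in limited form. The primary model as described does not compare arms within the site blocks used for randomisation, and its standard error is miscalibrated in a direction that depends on how sessions fill. With no session effect and an assumed site SD of 0.5, the type I error is about 4% with near-equal sessions and about 6% to 7% in a markedly unequal layout, against about 5% with site in the model. The shift in the realised contrast is chance imbalance, usually small.

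All these sizes rest on assumed site and session variances. With no site differences in change, the site part vanishes. The conclusion that site and session must be handled together does not depend on the site variance: whole sessions are randomised, three per arm, and a site term alone leaves session variation out of the standard error.

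**What to change.** State in the Statistical methods section that the primary model for each outcome includes site and site-by-time as fixed effects, jointly with a session-level random effect on change, with small-sample degrees of freedom. A simpler equivalent is to analyse the nine session mean changes with arm and site, on 4 residual df. If the full plan already does this, the article needs only a sentence to say so. Site should not be added without the session-level term.

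Site and session are known for every participant, so no new data are needed. The cost is precision on paper: the critical value rises from 1.99 (70 df, arm and site at participant level) to 2.78 (4 df), so intervals widen by 2.78/1.99, about 40%, at the same standard error, and by more if sessions vary. For a pilot that reports effect sizes, that width is an honest account of nine randomised sessions.
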